## Abstract

**Background:**

Patients with eating disorders (ED) typically report delays between the onset of symptoms and engagement with treatment services. Personal barriers including stigma, shame, and guilt, as well as the availability of social support may influence patients’ decisions to engage with treatment services. Patient narratives are personalized stories discussing the illness and recovery of previously affected persons. Such narratives can reduce self-stigma and provide current patients with hope for their own recovery.

**Method:**

This pilot study will examine the effects of patient narrative videos on the treatment motivation and uptake of treatment services for patients with ED. Three narrative videos were developed from the perspectives of (a) a former patient with an ED, (b) an ED specialist, and (c) the same former patient discussing a somatic condition unrelated to ED. Patients will be randomized into three video viewing and one treatment-as-usual group. Effects on treatment motivation will be assessed using the University of Rhode Island Change Assessment Scale (URICA-S) immediately after viewing the videos, as well as one-week and three-month follow-ups. Treatment uptake will be assessed during follow-up using a questionnaire listing possible treatment interactions. A post-intervention questionnaire and semi-structured interviews will be used to assess the feasibility and acceptability of patient narrative videos for this population.

**Discussion:**

There is an urgent need to encourage patients with ED to engage with specialized treatments as soon as possible. Patient narratives may be a pivotal approach to implementing cost effective and easy to disseminate early intervention programs to future patients with ED.

## Public significance statement

Currently, there exists an urgent need to close the treatment gap and encourage patients with eating disorders (ED) to engage with specialized treatment services as soon as possible. Narrative videos featuring the experiences and perspectives of former patients could be a pivotal approach to implementing cost effective and easy to disseminate early interventions to patients currently affected by ED.

## Introduction

Treatment for eating disorders (ED) has been shown to be most effective when initiated shortly after the onset of symptoms [1]. Nevertheless, patients typically report a significant delay between the onset of ED symptoms and their engagement with treatment services. The duration of untreated ED (DUED), i.e., the time between onset of the ED and first contact with treatment, ranges from 2.5 years for Anorexia Nervosa to 6 years for Binge-Eating-Disorder [2]. Longer DUED is associated with a progression of ED symptoms, increased psychological distress, and increased mortality among patients with Anorexia [2, 3]. Patients with ED often report long wait times and/or a lack of specialized treatment services as contributing to the DUED they experienced [4, 5]. Interventions such as the First Episode Rapid Early Intervention for Eating Disorders (FREED) service model in the UK aim to reduce these healthcare-related delays by optimizing the referral process for tailored and evidence-based ED treatment services [6]. Meanwhile, feelings of ambivalence or a lack of motivation from patients to change their behaviors have also been reported as contributing to the DUED of most EDs [7]. In fact, many patients will wait up to 12 months after recognizing their ED symptoms before deciding to seek treatment [7]. The Transtheoretical Model of Health Behavior Change (TTM) by Prochaska and Di Clemente [8] can be used to understand patients’ motivation (or lack thereof) to recover from their ED. The TTM proposes that when changing a health behavior, an individual will gradually progress through six stages of willingness to change, namely precontemplation, contemplation, preparation, action, maintenance, and termination. Evidence suggests that patients who have a higher motivation to change prior to commencing treatment (i.e., are further along the stages of change) will demonstrate better treatment outcomes, including reduced dietary restriction, binging, and purging behaviors [9, 10].

Engagement with treatment services may be influenced by the social support patients can rely upon [11, 12]. In fact, the presence [13, 14] or absence [15, 16] of social support may either facilitate or impede a patient’s decision to seek and/or engage with treatment services. Unfortunately, a common theme among individuals with ED is a general lack of social connections outside the immediate family, with many individuals utilizing websites and online forums in the hopes of finding support, acceptance, and a place of belonging among fellow ED patients [17]. Currently, there is an increased use of peers in the care of various mental disorders, including ED (e.g., [18, 19]). Peer mentorship programs with former and currently recovered ED patients have shown high engagement rates, as well as increased mood, quality of life, and hope for a possible recovery [20]. Similarly, information shared by fellow ED patients has been reported by patients to be significantly more empowering than when the same information was presented by healthcare professionals [21].

Patient narratives, i.e., personalized stories of persons previously affected by a mental disorder detailing their illness and recovery, provide another promising adjunct to ED treatments. Patient narratives are available both as published books and in a variety of formats throughout the internet [22, 23]. Studies have shown that reading patient narratives may reduce the self-stigma associated with ED in student populations [24] and, when presented in a safe and responsible way, may shorten the duration of DUED [25] and provide current patients with feelings of hope for a possible recovery [22]. However, to date only a handful of studies have investigated the effects of patient narratives in ED care [26]. Studies on other severe mental disorders, such as psychosis (e.g., [27, 28]), suggest that viewing patient narrative videos can increase self-efficacy and provide hope toward recovery. These effects were strongest after viewing videos featuring former patients, in comparison to videos featuring healthcare professionals, despite the presentation of identical recovery-oriented content [27]. Patients with psychosis typically report similar levels of ambivalence toward treatment as patients with ED [29], and these findings suggest that perceptions of similarity/authenticity allow former patients with lived experience to inspire hope for recovery among persons currently affected by the disorder [27]. Three further clinical trials are currently being completed as part of the Narrative Experiences Online (NEON) Study [30], in which the effects of patient narrative videos are being examined for persons experiencing psychosis and other mental health problems. To the best of our knowledge, no prior studies have examined the effects of evidence-based and recovery-focused patient narratives presented as videos for patients with ED.

## Study aims

The proposed study will examine the effects of patient narratives provided in video format for patients with ED. In particular, the role of patient narrative videos on patients’ treatment motivation and uptake of treatment services will be assessed. The study further aims to ascertain the feasibility and acceptability of patient narratives, as well as establishing data to identify suitable outcomes and sample size calculations for a larger trial.

Patients will be randomly assigned to view one of three narrative videos, presented from the perspective of a former and currently recovered patient with an ED (Video A), an ED specialist (Video B), and the same former patient reporting on a somatic condition unrelated to ED (Video C). It is expected that patients who receive access to narrative videos from the perspective of a former patient with an ED (Video A) or an ED specialist (Video B) will show:

stronger increases in treatment motivation (Hypothesis 1).and increased likelihood to engage in treatment uptake behaviors (Hypothesis 2).

compared to patients who receive access to a narrative video unrelated to ED (Video C) or patients who receive access to no videos.

It is further expected that patients who receive access to a narrative video from the perspective of a former patient with an ED (Video A) will show:

stronger increases in treatment motivation (Hypothesis 3).and increased likelihood to engage in treatment uptake behaviors (Hypothesis 4).

compared to patients who receive access to a narrative video from the perspective of an ED specialist (Video B).

## Method/design

This study protocol is reported according to the recommendations of the SPIRIT checklist [31].

### Study participants

Female patients with EDs who attend a consultation appointment at the outpatient services of the Department of Psychosomatic Medicine and Psychotherapy at the Medical University Hospital Tübingen will be informed about the study and invited to participate. During such consultation appointments patients complete a variety of diagnostic assessments and are provided with recommendations for treatment. Patients do not receive any counselling or treatment at these appointments. Patients will be asked to provide information about any previous treatment(s) they may have received and will be excluded if their last treatment occurred within the last four weeks prior to the start of the study. As the majority of patients begin experiencing EDs already in late adolescence, patients aged 15 years and older will also be recruited from the Child and Adolescent Psychiatry at the Medical University Hospital Tübingen. Patients with any full-syndrome or subclinical ED diagnosis will be invited to participate in this study to gain a better understanding of any transdiagnostic differences that may affect for whom this intervention is best suited. In order to further increase reach and diversity, the study will also be made available to individuals who seek obesity treatment at the Medical University Hospital Tübingen, provided they also display symptoms of an ED.

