### Inclusion criteria

Patients must comply with all of the following criteria in order to be eligible for the trial:

Full-syndrome or subclinical ED according to DSM-5 (diagnosed by a trained clinician).Minimum age 15 years.Female gender.Written informed consent.

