### Exclusion criteria

Acute suicidality.Psychotic disorders (lifetime).Bipolar disorder (lifetime).Current moderate-severe substance use disorders.Currently receiving ED treatment(s).

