## Conclusion

There is currently an urgent need to encourage and assist patients with ED to engage with specialized treatments as soon as possible. If effective, patient narratives may be a pivotal approach to implementing cost effective and easy to disseminate early intervention programs to future patients with ED.

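### The rationale and outlook are early intervention, but eligibility admits any illness duration and past treatment, so pooled uptake mixes first engagement with return to care, and the planned uptake test cannot use treatment history

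*Protocol article*

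**What the plan says.** **Rationale.** The Introduction says that ED treatment "has been shown to be most effective when initiated shortly after the onset of symptoms". It defines the duration of untreated ED as "the time between onset of the ED and first contact with treatment" and reports that it "ranges from 2.5 years for Anorexia Nervosa to 6 years for Binge-Eating-Disorder". It also cites work suggesting that narratives may shorten this duration.

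**Outlook.** The Conclusion presents narratives, conditionally, as a possible route to "implementing cost effective and easy to disseminate early intervention programs to future patients with ED". The Discussion part of the Abstract and the Public significance statement say much the same, also in hedged terms.

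**Eligibility.** Under Study participants, "Patients with any full-syndrome or subclinical ED diagnosis will be invited to participate in this study". Inclusion criteria give "Minimum age 15 years", with no upper age, no limit on illness duration and no first-treatment condition. Treatment history is restricted in two ways only: current ED treatment is an exclusion criterion, and patients "will be excluded if their last treatment occurred within the last four weeks prior to the start of the study".

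**Data and analysis.** Study participants and Self-report measures both have patients report previous treatment, and Main outcome measures takes uptake at T0, T2 and T3. The Treatment uptake behaviors analysis is a Pearson chi-square of group against uptake at those times. The Treatment motivation analysis is a mixed model that names group allocation only.

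**Limitations.** Strengths and limitations names selection through the recruitment setting. It mentions neither prior treatment nor illness duration.

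**The concern.** By the Introduction's own definition, the untreated period has already ended for anyone treated before, so a video cannot shorten it for her. Her attendance by T3 is a return to care, or follow-on care. A never-treated patient's attendance is the first contact that the rationale is about. The two are counted alike, and a result carried mainly by experienced patients could be read as support for early intervention.

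The article also describes the study as a pilot that should supply data for sizing a larger trial. If that trial were an early-intervention trial, uptake rates pooled over both kinds of patient could be the wrong planning figures. The chosen uptake test leaves no way to use the treatment history that the study collects.

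**Working it through.** **1. The plan's own figure.** Four groups of 25 give 4 × 25 = 100, as stated under Sample size. The article gives no power calculation and no share of previously treated patients, so the shares and effects below are assumptions. Uptake is taken as attendance at an appointment, following the definition under Self-report measures.

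**2. What a pooled effect can show.** Let s be the never-treated share. With similar shares in each arm, the pooled difference in uptake is

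D = s × D(never) + (1 − s) × D(prior).

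If s is below 1, a positive D is compatible with D(never) = 0. The eligibility rules allow any s, so D alone does not establish an effect on first engagement.

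**3. Precision to be gained by adjusting.** Assume attendance near 50%. With 25 per arm, the unadjusted standard error of a difference between two arms is

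SE = √(2 × 0.25/25) = 0.141, or 14.1 points.

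If a share p was treated before and prior treatment shifts attendance by d, it explains p(1 − p)d² of the variance of 0.25, and the adjusted SE is √(2 × (0.25 − p(1 − p)d²)/25).

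| p | d | variance explained | share of 0.25 | adjusted SE |
|---|---|---|---|---|
| 0.5 | 0.20 | 0.0100 | 4% | 13.9 points |
| 0.3 | 0.30 | 0.0189 | 7.6% | 13.6 points |
| 0.5 | 0.30 | 0.0225 | 9% | 13.5 points |
| 0.6 | 0.30 | 0.0216 | 8.6% | 13.5 points |
| 0.5 | 0.40 | 0.0400 | 16% | 13.0 points |

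The gain is real but small.

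**4. Precision of never-treated estimates.** Half-widths of 95% intervals for a two-arm difference, with n never-treated patients per arm, are 1.96 × √(2/n) in SD units for motivation and 1.96 × √(2 × 0.25/n) for uptake near 50%.

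| never-treated share | n per arm | motivation | uptake |
|---|---|---|---|
| 100% | 25 | 0.55 SD | 28 points |
| 75% | 18.75 | 0.64 SD | 32 points |
| 50% | 12.5 | 0.78 SD | 39 points |
| 25% | 6.25 | 1.11 SD | 55 points |

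Estimates this wide can describe the subgroup but cannot carry a test.

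**The case against.** **The aims fit the population.** Study aims and Main outcome measures concern motivation and uptake in patients with ED generally, and untreated duration is not an outcome. The rationale also rests on ambivalence, stages of change and social support. Strengths and limitations points to people who take no further step after a diagnostic appointment, which includes returning patients. This stands, and it is why eligibility need not change. Study participants justifies the diagnostic breadth by transdiagnostic differences but gives no reason for leaving illness duration and past treatment open.

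**Stronger readings.** A reader might infer that the protocol concludes that videos shorten untreated illness. It does not: the three forward-looking statements are conditional and speak of future programs. A reader might also infer that the trial cannot inform early intervention at all. That goes too far, because never-treated patients are eligible and identifiable from the baseline questionnaire. Nor is a chance difference between arms in treatment history a bias. Under randomization it is part of ordinary sampling error, about 9% of the variance in the central case above.

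**Baseline uptake is compared, and adjustment can be left to an analysis plan.** The article does compare uptake by group at T0, so an imbalance might be seen. Seeing it at T0 does not adjust the comparisons at T2 or T3. Adjustment is often left to an analysis plan, but here the article has fixed a test for uptake that cannot take a covariate.

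**Never/ever treated is not illness duration.** A woman ill for many years without treatment counts as never treated. This stands: the covariate addresses first engagement against return, and illness duration has to be handled in the limitations and wording.

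**Conclusion.** The mismatch between the early-intervention framing and the admitted population is in the text, and the limitations do not disclose it. A pooled uptake effect would show engagement or re-engagement in a mixed population. By itself it would not show an early-intervention effect.

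The consequence is mainly for interpretation and for planning the larger trial. The statistical cost of ignoring treatment history is modest: about 14.1 against 13.5 points of standard error in the central case, and 13.0 to 13.9 over the assumed range. These figures rest on attendance near 50%, 30% to 60% previously treated, and a shift of 20 to 40 points, none of which the article gives. The framing point needs none of these assumptions.

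**What to change.** 1. Keep eligibility broad.
2. For uptake at T2 and T3, replace the chi-square with a regression of uptake on group, adjusted for prior ED treatment (never/ever, from T0). Use a risk-difference model, or a logistic model with results standardized to risk differences. The precision gain above applies on the risk-difference scale, not to a logistic coefficient. At T2 the model covers the three video groups only, because Procedure assesses TAU at T0 and T3.
3. Add the same covariate to the motivation model, with its interaction with time. T0 scores are among the responses, so a main effect alone would shift the level and hardly touch the contrasts in change.
4. Report uptake and motivation by group and prior-treatment status descriptively, with intervals and no subgroup tests.
5. Add prior treatment and illness duration to Strengths and limitations. In the Abstract, Public significance statement and Conclusion, speak of engagement or re-engagement of patients at any stage of illness.

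**Cost.** No new data are needed. The uptake analysis changes from a simple test to a model, which may be strained by sparse cells at 25 per arm. The precision gain is small, the never-treated estimates will be imprecise, and the outlook becomes less sweeping.

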### Inclusion criteria

Patients must comply with all of the following criteria in order to be eligible for the trial:

Full-syndrome or subclinical ED according to DSM-5 (diagnosed by a trained clinician).Minimum age 15 years.Female gender.Written informed consent.

### Exclusion criteria

Acute suicidality.Psychotic disorders (lifetime).Bipolar disorder (lifetime).Current moderate-severe substance use disorders.Currently receiving ED treatment(s).

### Materials used

#### Self-report measures

Demographic and diagnostic information, including ED diagnosis, will be obtained from patient files. Patients will be provided with a definition of patient narratives before being asked if/what experiences they may have had with patient narratives, and in what format. The following questionnaires will be used to determine ED psychopathology, comorbid mental disorders, treatment motivation, previous and current treatment uptake behaviors, and hope and confidence toward recovery:

ED psychopathology will be assessed using the Eating Disorders Examination Questionnaire (EDE-Q [32]). The EDE-Q consists of 28 items measuring the cognitions and eating disturbances associated with ED, as well as diagnostically relevant behavioral features of ED. Items can be allocated to four subscales: Restraint, Eating Concern, Shape Concern, and Weight Concern. Mean subscale scores and a mean global score are calculated in order to determine overall eating pathology [32]. The EDE-Q has high internal consistency (α ≤ 0.97) and is sensitive to change [33].Comorbid mental disorders will be assessed using the Patient Health Questionnaire (PHQ-D [34]). The PHQ-D consists of 15 items and is used to screen for symptoms of depressive disorders, panic disorder, and psychosocial functioning. The PHQ-D has excellent criterion validity and good internal consistency for depressive disorders (α = 0.88) [34].Treatment motivation will be assessed using the University of Rhode Island Change Assessment Scale—Short Version (URICA-S [35]). The URICA-S consists of 16 items, measuring four of the six stages of change (i.e., Pre-contemplation, Contemplation, Action, and Maintenance) according to the TTM [8]. Readiness for change scores will be calculated for each patient by summing the mean contemplation, action, and maintenance subscale values of the URICA-S, before subtracting the mean precontemplation subscale value [36]. The URICA-S shows acceptable to good internal consistency (α = 0.61–0.85), as well as strong criterion validity [35].Treatment uptake behaviors will be assessed using a short questionnaire developed for this study. Patients will be asked to select from a list which treatment services they have previously or currently engaged with, and to what extent (e.g., phone contact, appointment made/attended). ED treatment services are varied, including inpatient, partial inpatient, and outpatient treatment in psychiatric/psychosomatic clinics, outpatient psychotherapeutic and nutritionist services, and digital eHealth interventions. For the purposes of this study, treatment uptake will be defined as attending appointments at any of these treatment providers, however, preparatory actions such as researching treatment options and time spent on the wait list will also be assessed.Hope and confidence toward recovery will be assessed using two visual analogue scales. Patients will be asked to indicate how hopeful and confident they are regarding their own recovery. Each patient’s scores will be calculated by measuring the distance (0-100 mm) on the visual analogue scales between the anchor (no hope/confidence) and the patient’s selection, with higher scores indicating greater hopefulness and confidence toward recovery.A post-intervention questionnaire will be used to assess patients’ feedback regarding the authenticity, empathy, and likeability of the person featured in the narrative video, as well as the usefulness of the video(s) as a whole. A subgroup of six patients (determined through Research Randomizer [37]) will also be invited to participate in a semi-structured interview to provide further insights into their perception of the authenticity, empathy, likeability, and usefulness of the video(s), so as to allow for a more thorough and qualitative understanding of how these are experienced by patients.

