### Outcomes

#### Main outcome measures

Main outcome measures of this study will be changes in patients’ treatment motivation and treatment uptake behaviors. Changes in treatment motivation will be measured by comparing patients’ baseline (T0) readiness for change scores (URICA-S) to scores immediately after viewing the videos (T1), at one-week (T2) and three months follow-up (T3). Changes in treatment uptake will be measured by comparing the amount of treatment seeking activities indicated at baseline (T0), at one-week (T2) and three months follow-up (T3).

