#### Treatment uptake behaviors

Pearson’s chi-square tests of contingencies will be used to assess the relationship between patients’ group allocation (IG1/IG2/CG/TAU) and treatment uptake behaviors at T0, T2, and T3.

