### Strengths and limitations

A strength of this study is the strong integration of lived experience into the intervention, which has been increasingly advocated [19, 38, 39]. A further strength is the inclusion of clinically relevant outcome measures, including treatment uptake behaviors at several time points in response to engagement with patient narratives. The inclusion of such measures will allow the results of this study to more easily translate into and inform clinical practice. The long follow-up period of three months is roughly in accordance with the average wait times for psychotherapeutic treatment in Germany [40, 41], although this varies depending on region, disorder, and type of service. The study design will allow both short-term and long-term effects of this intervention to be examined. Limitations of this study include a selection bias, as the recruitment focuses on patients attending a diagnostic appointment at the Medical University Hospital Tübingen. Nevertheless, a large proportion of persons who attend such appointments fail to undertake any further actions, and therefore may benefit greatly from this intervention.

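### Treatment arranged before T0 can count as uptake at T3, and the uptake test takes no account of it: no bias, but a diluted effect and lost precision

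*Protocol article*

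**What the plan says.** All references are to the protocol article.

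- **Definition of uptake** (Self-report measures): "treatment uptake will be defined as attending appointments at any of these treatment providers". The same paragraph adds that "preparatory actions such as researching treatment options and time spent on the wait list will also be assessed". The questionnaire also asks how far each contact went and separates an appointment made from one attended.
- **Eligibility**: the exclusion criteria remove patients now in ED treatment. Study participants adds that patients "will be excluded if their last treatment occurred within the last four weeks prior to the start of the study". Neither rule mentions a waiting-list place or a future appointment.
- **Outcome** (Main outcome measures): change in uptake compares the amount of treatment-seeking activity reported at T0 with that at one week (T2) and three months (T3).
- **Test** (Treatment uptake behaviors, under Statistical analyses): "Pearson’s chi-square tests of contingencies will be used to assess the relationship between patients’ group allocation (IG1/IG2/CG/TAU) and treatment uptake behaviors at T0, T2, and" (the sentence ends with the three-month visit). No baseline variable enters.
- **Follow-up** (Strengths and limitations): the three-month period "is roughly in accordance with the average wait times for psychotherapeutic treatment in Germany".

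**The concern.** Hypotheses 2 and 4 (Study aims) say that a video makes patients more likely to engage in treatment uptake behaviours. A patient who booked before T0 and attends in month two is counted as uptake, although she arranged it before randomisation. If the average wait is about three months, a patient already waiting at T0 is well placed to attend by T3. A patient whom the video prompts to start looking may still be waiting then. The T3 outcome can therefore partly record decisions that no video could have caused.

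At stake is how readable one of the two main outcomes is. The pilot is also meant to supply data for the sample size of a larger trial (Sample size section). A pooled uptake rate that mixes two kinds of patient is a weak basis for that unless the mix is known.

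**Working it through.** **The plan's own figure.** 4 groups × 25 = 100, which matches the stated total. The article gives no uptake rate, effect size, power or pre-booked share, so there is no power calculation to reproduce.

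**Does the comparison with T0 remove the problem?** A booked patient has made an appointment at T0 but has not attended it. At T3 she has attended. On the attendance definition she changes from no to yes, exactly like a patient who first sought help after the video. The answer is no.

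**Dilution.** Let w be the share with treatment already arranged at T0, q their attendance by T3 (the same in every arm), and p_C and p_T the attendance of the others without and with an effective video.

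Difference = [wq + (1−w)p_T] − [wq + (1−w)p_C] = (1−w)(p_T − p_C)

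Assumed, not in the article: q = 90%, p_C = 25%, p_T = 50%.

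| w | Control arm | Video arm | Difference |
|---|---|---|---|
| 0 | 25.0% | 50.0% | 25.0 points |
| 10% | 0.09 + 0.225 = 31.5% | 0.09 + 0.45 = 54.0% | 22.5 |
| 20% | 0.18 + 0.20 = 38.0% | 0.18 + 0.40 = 58.0% | 20.0 |
| 30% | 0.27 + 0.175 = 44.5% | 0.27 + 0.35 = 62.0% | 17.5 |

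Other assumptions shrink by the same factor. With 20% versus 50% in the unbooked, 30 points become 27 at w = 10% and 21 at w = 30%. With q = 90%, the number per arm for 80% power (two-sided 5%) then rises from 39 to 51 and 88.

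**Precision.** Take w = 30% and no video effect, so uptake is 44.5% in both arms. The standard error of the difference at 25 versus 25 is √(2 × 0.445 × 0.555/25) = 14.1 points. It has two parts:

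- chance imbalance in the number pre-booked: √(2 × 0.3 × 0.7/25) × (0.90 − 0.25) = 8.4 points
- variation within the two kinds of patient: √(2 × [0.3 × 0.09 + 0.7 × 0.1875]/25) = 11.3 points

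Check: √(11.25² + 8.42²) = 14.1. Stratifying on the T0 flag removes the first part. With no pre-booked patients the standard error would be √(2 × 0.25 × 0.75/25) = 12.2 points.

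**Power at w = 30%.** Normal approximation, two-sided 5%: power = Φ[(Δ − 1.96·SE₀)/SE₁], where SE₀ is the null standard error and SE₁ the one under the alternative.

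- *Unadjusted, 25 per arm*: Δ = 0.175, SE₀ = √(2 × 0.5325 × 0.4675/25) = 0.141, SE₁ = √([0.445 × 0.555 + 0.62 × 0.38]/25) = 0.139. Power is 23%.
- *Stratified, 25 per arm*: Δ = 0.7 × 0.25 + 0.3 × 0 = 0.175, SE₀ = √([0.7 × 2 × 0.375 × 0.625 + 0.3 × 2 × 0.9 × 0.1]/25) = 0.124, SE₁ = √([0.7 × 0.4375 + 0.3 × 0.18]/25) = 0.120. Power is 29%, or 31% if SE₁ is used throughout.
- *Restricted to the unbooked, 0.7 × 25 = 17.5 per arm*: Δ = 0.25, SE₀ = √(2 × 0.375 × 0.625/17.5) = 0.164, SE₁ = √(0.4375/17.5) = 0.158. Power is 33%.

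Stratifying recovers precision but leaves the 17.5-point average difference as it is. The 25-point difference appears only in the unbooked subgroup.

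**The case against.** Four points on the other side carry weight.

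1. **The share may be modest.** Recruitment is at a consultation that gives a diagnosis and treatment recommendations, and Strengths and limitations says that many who attend take no further step. A reader might infer from the three-month average wait that many attendances by T3 were arranged before T0. An average wait does not show how many patients are waiting at T0. This stands: the size is unknown.
2. **Chance imbalance is not an extra harm.** A reader might take the 7 to 8 points of imbalance (7.4 at w = 20%, 8.4 at w = 30%) as a route to a false video effect. It is already inside the ordinary 14-point standard error, and the chi-square test allows for it. Any prognostic baseline factor behaves this way. This stands in full.
3. **Booked patients can still respond.** A reader might infer that their outcome was settled beforehand. They can keep or drop the appointment, and keeping it fits the wording of Hypotheses 2 and 4. Replacing attendance by new contact, or making the unbooked subgroup the main comparison, would ask a narrower question. This stands as a reason to keep the attendance definition.
4. **It is a pilot, and the analysis plan may deal with it.** This stands in part. No confirmatory uptake test is claimed, and how a baseline flag is used is often left to the analysis plan. But the article itself fixes the definition and names an unadjusted test, uptake is a main outcome, and the data are to inform a larger trial.

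**Conclusion.** The point holds in a limited form. Patients with treatment arranged before T0 are eligible, their later attendance counts as uptake, and neither the comparison with T0 nor the named test separates them. The consequence is dilution by the factor (1 − w) and some lost precision.

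The article does not support a claim of systematic bias between arms or of type I error inflation, because allocation is random and the flag is a baseline characteristic. Nor does it support a claim that most uptake was decided beforehand.

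The 22.5, 20.0 and 17.5 points rest on assumed attendance of 90%, 25% and 50%, on equal attendance of booked patients in every arm, and on assumed pre-booked shares of 10% to 30%. If few patients are pre-booked at T0, the effect is small. The case for acting is that the information appears to be collected already and the change is cheap. It does not make the uptake comparison well powered: in the 30% illustration, power stays near 30% either way.

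**What to change.** - From the T0 items on appointments made and wait-list time, flag each patient with ED treatment already arranged, and report the share by arm.
- For Hypotheses 2 and 4, keep all randomised patients and the attendance definition. Replace the unadjusted chi-square at follow-up by a comparison stratified by or adjusted for the flag, such as a Cochran-Mantel-Haenszel test or logistic regression.
- As supporting analyses, report uptake in patients with nothing arranged at T0 (a baseline subgroup, so the randomised comparison is kept) and contact newly initiated after T0. The second also picks up patients prompted by the video who are still waiting at T3.
- Carry the pre-booked share and both sets of rates into the sample size planning of the larger trial.

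Cost: some analysis wording and slightly more work. Strata will be small at 25 per arm, so one two-level flag is enough. Eligibility, the videos and the visits do not change.
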